#### Experienced changes

The interview transcripts of the clients’ experiences of the intervention process in SEE will be analysed using grounded theory [106] to uncover the characteristics and meanings of interactions in the process.

#### Potential SEE outcomes

Patterns of changes within the group will be determined by descriptive statistics, comparison and non-parametric tests on all the outcome measures (POES, OBQ, Oval- PD, LiSat-11, GSE, WAI) and, also, by goal achievement. The data will be analysed over time (from baseline to 4 months and 12 months). To determine the variability between the outcomes (at 4 months and 12 months) and background data, logistic regression will be used for dichotomous outcomes and linear regression will be used for continuous outcomes. The statistical calculations will be performed with SPSS version 27.0 [107] and the *p*-value will be set to *p* <0.05 for all statistical tests.

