## Methods/design

### Study design

This feasibility study is based on a pretest posttest design without a control group to evaluate aspects of feasibility and potential results of the SEE programme. The data collection comprises outcome measurements/assessment tools, qualitative interviews, focus groups and descriptive quantitative data from feasibility registration forms. Consequently, quantitative and qualitative data will be collected concurrently embedded in a mixed-method design of the entire study.

This study, including the SEE programme, follows the Medical Research Council (MRC) guidelines [40, 44] for how complex interventions are developed and evaluated through research in four phases. The present study of the SEE programme involves the second phase of research developing complex interventions, and the design is based on guidance in the area [41, 42, 45]. The study protocol for this feasibility study follows “the Standard protocol items: recommendations for intervention trials 2013 statement” (SPIRIT) [46, 47]. The description of the intervention follows the “template for intervention description and replication” (TIDieR) [48]. The study is also based on guidelines for process evaluation [44], identifying aspects important for sustainability of the implementation in relation to different contexts.

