### Sample size

As this is a feasibility study, no power calculation is required [41, 85]. The sample size justification is instead based on the premises that the sample has to be sufficiently large to provide enough detail and information on the intervention. That is, on the aspects of feasibility investigated and potential outcomes [41]. It is important that the sample is representative of the target population. Additionally, as the OTs will become experienced in applying the new programme and providing Internet-based interventions the required sample size is estimated to be 30–40 clients with stroke.

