#### Potential SEE outcomes

The potential outcomes of SEE will be determined using the following standardised assessment tools; The Profiles of Occupational Engagement [91] is based on an interview of a 24-h completed diary of time use. The nine items are scored on an ordinal scale and a higher score indicate a higher level of engagement in daily activities. The Occupational Balance Questionnaire (OBQ) [92] consist of 11 items that are summed to a total score, ranging between 0 and 33. A higher score implies more satisfaction with the amount and variation of occupations, i.e., a higher level of occupational balance. The Occupational Value predefined (Oval-Pd) [93] includes18 items that are summed into a general occupational value, ranging between 18 and 72. A higher score indicates that the respondent is frequently engaged in valued daily activities. The Life Satisfaction Questionnaire (Lisat-11) [94, 95] consist of 11 items, including self-reports of satisfaction with life as a whole and physical and mental health. The items are rated on ordinal scale ranging from 1 to 6 and a higher score reflect a higher level of satisfaction. How self-management is realised will be assessed using the General Self-Efficacy Scale (GSE) [96, 97] that includes 10 items that are summarized to a score ranging between 10 and 40. A higher score reflects greater sense of general self-efficacy. Actual and perceived work ability will be evaluated for those of working age. The Work Ability Index (WAI) [98] examines self-perceived work ability on a 10-point ordinal scale. A higher score reflects a higher level of perceived work ability. Goal achievement in the activity plan will be noted by the OTs.

Sociodemographic data will be collected using a registration form. To evaluate aspects of the medical disorder, the Glasgow Outcome Scale Extended (GOSE) [86], Mental Fatigue Scale (MFS) [99] and Hospital Anxiety and Depression Scale (HAD) [87] will be used at baseline.

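### A flat p<0.05 on every test, not labelled exploratory, is a poor basis for judging change in 30–40 clients: significant and non-significant results can both mislead

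*Protocol article*

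**What the plan says.** All references are to the protocol article.

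- **Analysis, Potential SEE outcomes.** Change within the group is to be determined by descriptive statistics, by comparison and by "non-parametric tests on all the outcome measures (POES, OBQ, Oval- PD, LiSat-11, GSE, WAI"), and also by goal achievement. On timing: "The data will be analysed over time (from baseline to 4 months and 12 months"). For the relation to background data, "logistic regression will be used for dichotomous outcomes and linear regression will be used for continuous outcomes". The threshold is "<0.05 for all statistical tests". No lead measure is named, no specific non-parametric test is named, and the tests are not described as exploratory.
- **Sample size.** "As this is a feasibility study, no power calculation is required"; on grounds of sufficient detail and information, "the required sample size is estimated to be 30–40 clients with stroke".
- **Study design.** A "pretest posttest design without a control group".
- **Outcomes, Potential SEE outcomes.** "Actual and perceived work ability will be evaluated for those of working age", so the WAI may have fewer respondents than the other measures.
- **Objectives.** The second objective is to establish which measures and tools pick up change. The third concerns how variable the potential outcomes are.
- **Discussion.** Going on to a pilot RCT is tied to confirmed feasibility together with results showing positive changes in daily activities.

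**The concern.** The study is sized for information about feasibility, not for hypothesis tests. Omitting a power calculation is acceptable on that footing. The difficulty is that the same plan then fixes a single significance threshold for every test and does not say that the resulting p-values are exploratory.

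Two later decisions could draw on those results: which measures to carry forward, and whether to proceed to a pilot RCT. With many tests at 0.05, a significant measure may be a chance finding. With 30–40 clients, a non-significant measure may have moved by an amount the study could not reliably detect. The WAI could look less responsive than the others simply because fewer clients answer it.

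**Working it through.** **Plan's own figure.** The 30–40 clients come with no effect size, SD, power or dropout allowance, so there is no calculation to reproduce.

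**Inputs from the document.** Six measures; two follow-up times; threshold 0.05 for each test; n = 30–40 in one group.

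**Assumptions.** Tests are two-sided (sidedness is not stated). The number of tests is inferred: either one omnibus test per measure (6) or one test per measure and follow-up time (6 × 2 = 12). Regressions and goal achievement would add to either count, by an amount that is not stated.

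**1. False positives if no measure truly changes.** For k independent tests, P(at least one) = 1 − 0.95^k.
- k = 6: 1 − 0.95^6 = 0.265.
- k = 12: 1 − 0.95^12 = 0.460; expected number 12 × 0.05 = 0.6.
- k = 12, correlated. In a simulation of 400,000 draws from a 12-variate normal, the chance was 0.43 (assumed correlation 0 between measures, 0.5 between times), 0.35 (0.5 and 0.5) and 0.26 (0.7 and 0.7).

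The range is therefore about 26–46%.

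**2. Power of one unadjusted test.** A paired noncentral t was used with effective size 0.955n (the efficiency of the Wilcoxon signed-rank test under normality). The noncentrality is d√(0.955n), where d is the mean change divided by the SD of change. For n = 30 and d = 0.3 it is 0.3 × √28.65 = 1.61, giving power 0.34.

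| Pairs | d = 0.2 | d = 0.3 | d = 0.5 | d = 0.8 | d at 80% power |
|---|---|---|---|---|---|
| 30 | 0.18 | 0.34 | 0.73 | 0.98 | 0.54 |
| 40 | 0.23 | 0.44 | 0.85 | >0.99 | 0.47 |

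**3. Fewer pairs.** With 20% attrition (assumed), 30 × 0.8 = 24 and 40 × 0.8 = 32 pairs remain, and the detectable d becomes 0.61 and 0.52. If only 20 clients supply WAI data (assumed), it is 0.68.

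**4. What estimation would give.** The 95% CI half-width for a mean change, in SD of change, is t(0.975, n−1)/√n. This is 2.045/√30 = 0.37 for n = 30 and 2.023/√40 = 0.32 for n = 40.

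**5. What a correction would do instead.** Bonferroni over 12 tests uses 0.05/12 = 0.0042. Power at d = 0.5 then falls to 35% (n = 30) or 52% (n = 40), and the detectable d rises to 0.75 or 0.64.

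**The case against.** The best defence is that this is an uncontrolled feasibility study whose outcomes are called potential throughout. No confirmatory claim is planned, and exploratory tests need neither a power calculation nor a multiplicity adjustment. Interval estimates and test details may also sit in a full protocol or SAP that is not shown. Much of this stands: the missing power calculation and the lack of an adjustment are not faults in themselves. It does not remove the point, because the article states one threshold for all tests and gives them no exploratory status.

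Three stronger readings are tempting, and the document does not support them.

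- *The plan yields only p-values.* It does not. The same sentence lists descriptive statistics first and adds goal achievement.
- *Measures will be dropped for non-significance.* No section says so. Under Analysis, Feasibility of the intervention, the suitability of the tools is judged by a descriptive, content-analytic comparison with clients' experiences. Test results may inform that comparison, but they are not its stated criterion.
- *LiSat-11 will be tested item by item, multiplying the tests.* The Outcomes section describes its items without a summed total, but nowhere says that items are tested separately.

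The Discussion likewise gives no p-value rule for progression. It requires feasibility as well as positive change, and the next step is only a pilot RCT.

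**Conclusion.** The point holds in a limited form. A universal, unlabelled p<0.05 is a weak basis for determining change at this sample size, and results on either side of it can mislead. If nothing truly changes, the chance of at least one spurious positive is about 26–46%. Power is about 34–44% for a change of 0.3 SD, and the detectable change is about 0.47–0.54 SD with complete data.

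These figures rest on an inferred test count, two-sided tests, approximate normality of the change scores and, for the upper end of the false-positive range, independence. The false-positive figures also assume no true change on any measure. It would be too strong to say that the results must mislead: power is 85% for 0.5 SD at n = 40 and 98% for 0.8 SD at n = 30. Separately, without a control group even a genuine change cannot be attributed to SEE, whatever its p-value.

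This should be corrected, but it does not threaten the study.

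**What to change.** In Analysis, Potential SEE outcomes, make estimation the basis for judging change. For each measure at 4 and 12 months, report the median (Hodges–Lehmann) or mean change with a 95% CI, the SD of change and the number of pairs. State that any p-values, including those from the regressions, are exploratory, and that p<0.05 will not be used to judge measures or progression.

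This gives the size, spread and completeness of change that the second and third objectives need, and it is directly usable in planning the pilot RCT. A multiplicity correction is not the remedy, since it would reduce power that is already low.

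The cost is one or two sentences and no new data. The downside is fewer results to report as significant.

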Consistent with guidelines [39–43] on how complex interventions are developed, several uncertainties must be initially addressed in a feasibility study before moving to larger scale studies. The *clinical uncertainties* are related to the novelty of SEE, in using an Internet-based intervention after stroke [32, 34, 35] and of focusing on self-reflection and self-initiated management strategies for engagement in daily activities. In addition, it also involves as to what changes can be identified in clients after having completed the intervention. Thus, as SEE is an innovative approach, it is important to investigate its acceptability, adherence and value from the perspectives of clients and staff as this may inform potential modifications in the next version of SEE. *Methodological uncertainties* relate to research design concerns, whether the selected assessment tools are appropriate to guide the intervention and evaluate the outcome as well as the variability in outcomes and the relationship to client characteristics. Such knowledge, about the outcome of SEE for different groups, is important when future research design is planned and implemented. These clinical and methodological uncertainties must be addressed in a feasibility study.

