### Objectives

The overall aim is to evaluate the feasibility of the Internet-based occupational therapy intervention programme SEE. Specifically, this feasibility study aims to:Determine the acceptability, adherence and value of SEE for clients and staff involved in implementing SEEDetermine the outcome measures and assessment tools to identify changes in clients’ everyday life at 4 and 12 months after completing SEEDetermine the variability in the potential outcomes of SEE for the clients, and establish the relationship between the clients’ characteristics and scores at onset of SEE.Determine the changes experienced by clients in everyday life after SEE and their perceptions of the values of participating in the SEE.Determine clients’ experiences of adopting self-management strategies during the intervention process of SEE and determine what facilitates or hinders their adoption of strategies?

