### Participant timeline

Enrolment of the 30–40 client participants begun in November 2020 and is expected to be completed by June 2022. Due to the person-centred format of the programme, involving a change process, the length of the intervention process with the OTs is expected to vary between 3 and 5 months. However, the participants’ change process is expected to continue up to 1 year after the intervention started [84], which explains why outcome measures will be conducted up to 12 months after starting the intervention.

The outcome measures and sociodemographic data will be conducted at baseline before the programme is initiated (0 months), and outcome measures will be further conducted at 4 and 12 months after the intervention starts. The feasibility registration forms and logbooks will be completed by the OTs for each client participant after each session throughout the intervention process. The study-specific feasibility questionnaires will be collected from the client participants after 4 and 12 months. The individual interviews with the clients will be conducted 1 and 4 months after entering the SEE. Focus group interviews with OTs will be performed on three to four occasions scheduled at random times during the study period. The focus groups with the management and other keypersons/stakeholders will occur one to two times after the intervention has been completed.

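### The regressions of 4- and 12-month outcomes on background data do not name the baseline score of the same measure, so as written they mix starting level with change

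*Protocol article*

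**What the plan says.** The regressions are described in the protocol article under Analysis, Potential SEE outcomes. Their purpose is given as "To determine the variability between the outcomes (at 4 months and 12 months) and background data", and their form as "logistic regression will be used for dichotomous outcomes and linear regression will be used for continuous outcomes". The significance level is 0.05 for all tests. The term background data is not defined there or elsewhere.

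The same paragraph has a separate analysis of change: "The data will be analysed over time (from baseline to 4 months and 12 months"). It concerns patterns within the group, by descriptive statistics and non-parametric tests. It is not broken down by client characteristic.

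Three other places bear on the point:

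- **Objectives, third aim.** It asks for the variability in potential outcomes, and to "establish the relationship between the clients’ characteristics and scores at onset of SEE".
- **Background.** One methodological uncertainty is "the variability in outcomes and the relationship to client characteristics". Knowledge of the outcome for different groups is said to matter for planning future research.
- **Participant timeline.** "The outcome measures and sociodemographic data will be conducted at baseline before the programme is initiated (0 months"). Outcome measures and sociodemographic data are named as two separate things. The data-collection section does the same: after the outcome tools, a new paragraph begins "Sociodemographic data will be collected using a registration form" and adds GOSE, MFS and HAD at baseline.

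**The concern.** On the natural reading, background data means the sociodemographic form and perhaps GOSE, MFS and HAD. The baseline values of POES, OBQ, Oval-PD, LiSat-11, GSE and WAI would then be outside the models, although they are collected.

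A follow-up score is the starting score plus the change. If a characteristic goes with a low starting score, it will tend to go with a low follow-up score too, even when clients with and without it change alike. HAD and LiSat-11 are a plausible pair: one measures anxiety and depression, and the other includes satisfaction with mental health. A regression of 12-month LiSat-11 on HAD alone could then show an association that was already present before the programme began.

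The study wants to know how outcomes differ between groups of clients so that a pilot RCT can be designed. If pre-existing differences are read as differences in response, the wrong subgroups may be targeted or excluded in that trial.

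**Working it through.** **Inputs from the protocol article.** Sample size 30–40, single group (Sample size). Significance level 0.05 (Analysis); sidedness is not stated, and two-sided is assumed here. The article gives no correlation, SD or effect size, so there is no planned figure to reproduce.

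**Assumed inputs.** Let X be a characteristic, Y0 the baseline score and Y1 the follow-up score, with X and Y0 standardised. The correlation of X with Y0 is *a* = 0, 0.3 or 0.5. The baseline–follow-up parameter is *r* = 0.5 or 0.7. There is no dropout. Each cell has 20,000 simulated studies.

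**Scenario 1: X adds nothing once baseline is known.** Y1 = r·Y0 + √(1−r²)·e, so the correlation of Y0 with Y1 is r and that of X with Y1 is a·r. Share of studies in which X is significant:

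| n | a | r | a·r | Y1 on X | Y1 on X and Y0 | Y1−Y0 on X |
|---|---|---|---|---|---|---|
| 30 | 0 | 0.5 | 0 | 5.0% | 4.9% | 4.9% |
| 30 | 0.3 | 0.5 | 0.15 | 12.5% | 5.1% | 12.5% |
| 30 | 0.3 | 0.7 | 0.21 | 19.9% | 5.1% | 9.0% |
| 30 | 0.5 | 0.5 | 0.25 | 27.2% | 5.2% | 26.7% |
| 30 | 0.5 | 0.7 | 0.35 | 48.5% | 4.8% | 18.0% |
| 40 | 0 | 0.5 | 0 | 5.3% | 5.1% | 5.0% |
| 40 | 0.3 | 0.5 | 0.15 | 15.3% | 5.1% | 14.8% |
| 40 | 0.3 | 0.7 | 0.21 | 25.7% | 5.0% | 10.8% |
| 40 | 0.5 | 0.5 | 0.25 | 35.1% | 5.1% | 34.7% |
| 40 | 0.5 | 0.7 | 0.35 | 61.4% | 5.0% | 22.5% |

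With a = 0 and r = 0.7 all three models also give 4.7–5.1%.

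*Check by Fisher's z.* For a·r = 0.15 and n = 30: atanh(0.15)·√27 = 0.151 × 5.196 = 0.785, giving a rejection rate of about 12%. For a·r = 0.35 and n = 40: atanh(0.35)·√37 = 0.365 × 6.083 = 2.22, giving about 60%. Both agree with the table.

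**Scenario 2: change is independent of X and of baseline.** Y1 = Y0 + √(2(1−r))·e. Here the baseline–follow-up correlation is 1/√(3−2r), that is 0.71 and 0.79 for the two values of r. With a = 0.3 or 0.5, Y1 on X alone is significant in 20–73% of studies. With Y0 added the figure is 4.8–5.1%.

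**A change score as the response.** It holds the 5% level in scenario 2, but gives 9–35% in scenario 1 when a > 0. It is not a safe substitute for the covariate.

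**Precision for X in scenario 1.** The variance of the X coefficient with baseline, relative to without, is approximately (1−r²) / [(1−a²)(1−a²r²)].

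- a = 0.3, r = 0.7: 0.51 / (0.91 × 0.956) = 0.59; the standard error falls by 23%.
- a = 0.3, r = 0.5: 0.75 / (0.91 × 0.978) = 0.84; it falls by 8%.
- a = 0.5, r = 0.7: 0.51 / (0.75 × 0.878) = 0.78; it falls by 12%.
- a = 0.5, r = 0.5: 0.75 / (0.75 × 0.938) = 1.07; it rises by about 3%.

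**The case against.** **The omission is inferred.** Background data is undefined, nothing excludes the baseline score, and the third objective's reference to "characteristics and scores at onset of SEE" may mean that onset scores belong among the predictors. A condensed article may also leave its covariate list to a fuller document. This stands as far as intent goes: a reader might infer that the investigators decided against adjustment, and the text does not support that. It does not remove the point, because the article states both response and predictors, and they do not match the objective. If onset scores are meant as predictors, the analysis does not name them. If the aim is the relation between characteristics and onset scores, regressions of 4- and 12-month outcomes do not address it.

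**The target may be outcomes, not change.** In the simulation X really is correlated with follow-up, so the unadjusted rejections are correct detections of a marginal association. This also stands. They mislead only when read as a difference in response to the programme. Given the wish to know the outcome of SEE for different groups, that reading is close at hand.

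**The point does not reach every regression.** Goal achievement has no baseline score, and a characteristic unrelated to baseline raises no problem. Both are right.

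**Adjustment may not buy precision.** A reader might infer from r² that adjustment removes a quarter to a half of the residual variance and narrows the intervals to match. That ignores what X already explains and its collinearity with baseline. The gain for X is modest and can vanish.

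**Conclusion.** The point holds as a gap between the stated analysis and the stated objective. The regressions do not name the baseline score of the same measure, although it is collected. Under the assumed correlations of 0.3–0.5 and 0.5–0.7, with 30–40 clients and no dropout, a characteristic unrelated to follow-up given baseline is flagged in about 12–61% of studies, against about 5% with adjustment. At zero correlation with baseline there is no inflation. The range depends on these assumptions, since the documents supply no values.

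Three stronger readings are not supported:

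- A reader might infer that the models show who started high and not who changed. An unadjusted follow-up score reflects both.
- A reader might infer that adjusted models would show who benefits from SEE. With one group and no control, they show who changed, whatever the cause.
- A reader might infer that ordinal scores will be dichotomised. The text assigns logistic regression to dichotomous outcomes and does not say that other scores will be cut.

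This is a worthwhile correction in an exploratory feasibility study. It does not threaten the study as a whole.

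**What to change.** In Analysis, Potential SEE outcomes:

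1. List the variables that make up background data.
2. State that each 4- and 12-month model for a measure with a baseline value includes the baseline score of that measure plus one or two characteristics. Goal achievement is modelled without a baseline score.
3. Say which reading of the third objective is meant. If the relation between characteristics and onset scores is itself of interest, give it its own analysis.
4. State that coefficients describe differences in follow-up between clients with the same starting score, and are not evidence of change caused by SEE.

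The cost is a few sentences and one degree of freedom per model. No new data are needed. With 30–40 clients, and fewer for WAI because work ability is assessed only in those of working age, the limit on characteristics per model matters as much as the baseline term.
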